### Study Design and Objectives

In this pilot study, we aimed to evaluate the administration of 2 different synbiotic formulations compared to placebo in newborns in PNG during the first week of life. The study design was a double-blind, randomized, placebo-controlled trial in which newborns received 1 of 2 synbiotic formulations or a placebo over 7 consecutive days, with the first dose given before the newborn was aged 72 hours and administration completed within the first 10 days of life. The overall objective is to generate data that will inform the design and implementation of a larger, definitive clinical trial in infants in PNG, including the assessment of clinical end points.

The primary pilot study objectives were (1) safety in terms of intolerance (diarrhea, vomiting, abdominal distension, and weight gain) or probiotic sepsis during the 7-day supplementation period, leading to the cessation of the study medication; and (2) the feasibility and cultural acceptability of daily probiotic administration (the proportion of children who received all 7 daily doses of supplementation without missing any). The secondary objective was to demonstrate the colonization of the gut by probiotic strains at age 1 week and at ages 1, 3, 4, and 6 months. The exploratory objectives included (1) hospitalization rates until age 6 months, (2) nasopharyngeal carriage of *Streptococcus pneumoniae* and other respiratory tract bacteria at age 2 weeks and at ages 1 and 4 months, (3) immunoglobulin G (IgG) antibody responses to childhood vaccination (PCV13; diphtheria, tetanus, and whole-cell pertussis [DTwP]; *Hemophilus influenzae* type b [Hib]; and hepatitis B), (4) the kinetics of probiotic colonization at various time points over the first 6 months of life, and (5) maternal carriage and colonization by probiotic species and pathogens at the time of delivery.

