### Specimen Collection

For the secondary and exploratory objectives of the study, a number of biological samples were collected at several time points throughout the study (Figure 1). Rectal swabs and stool samples were collected to assess intestinal colonization by probiotic species. Rectal swabs were collected at enrollment; on the day of the last intervention administration (age 7-10 d); and at ages 2 weeks, 1 month, 3 months, 4 months, and 6 months. For sample collection, the infant was carefully placed face down across the mother’s thighs. A FLOQSwab (Copan Diagnostics) was gently inserted approximately 2 cm into the anal canal, rotated slowly for 10 seconds, then removed and placed into a tube containing eNAT preservation and transport medium (Copan Diagnostics). The swab was broken at the breakpoint, leaving the tip in the tube, which was then sealed and mixed by inverting 10 times. Stool samples were collected in addition to rectal swabs if infants passed stool during the study visit to allow for sensitivity comparisons of probiotic strain detection in rectal swabs versus stool. Stool samples were taken from infants’ diapers using a scoop and placed into stool specimen containers for storage and transportation. Upon arrival at the PNGIMR laboratory, stool samples were transferred to cryovials by laboratory staff. Both rectal swabs and stool samples were then stored at −80 °C.

Nasopharyngeal swabs to assess bacterial carriage and load were collected at ages 2 weeks, 1 month, and 4 months using FLOQSwabs. At each time point, 2 swabs were collected per infant when possible. For each collection, a swab was inserted horizontally into the nostril to collect a superficial mucosal sample from the anterior nares, advancing gently until resistance was met. The swab was then rotated while counting to 5 (or for approximately 3 s) before being removed. One swab was placed in skim milk tryptone glucose glycerol broth (STGGB) for culturing of bacterial pathogens (priority), and the second was stored in PrimeStore molecular transport medium (Thermo Fisher Scientific) for deep sequencing. Both samples were stored at −80 °C.

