Venous blood (maximum 2 mL at visits 1 and 2 and maximum 4 mL at visits 9 and 12) and saliva (visits 1, 7, 9, and 12) samples were obtained to assess systemic and mucosal vaccine responses and identify intervention-associated pathways or markers of immune maturation using systems biology approaches. Blood was collected using small 20-gauge butterfly needles and syringe techniques to reduce the risk of vein collapse. A maximum of 2 attempts were made to obtain a blood sample at each visit; if unsuccessful, no further attempts were made. For systems biology studies, we collected up to 2 mL of blood in heparin tubes. These samples were processed at the PNGIMR laboratory within 15 minutes of collection for RNA (transcriptomic analysis), plasma (proteomic and metabolomic analysis), flow (single cell immunophenotyping), and white blood cells (proteomic, metabolomic, and epigenetic analysis), following a protocol established by the Expanded Program on Immunization Consortium [32]. For serology, we collected up to 2 mL of blood in standard serum tubes, and the serum was separated and stored in cryovials by laboratory staff. Blood for serology was prioritized at ages 1 and 4 months over blood for systems biology. Saliva samples were collected from infants, ideally at least 30 minutes after being breastfed, using 4 to 6 surgical eye spears (Defries Industries) placed on the floor of the mouth to absorb saliva from the gums until saturated. The eye spears were then transported in 15 mL Falcon tubes (Corning Incorporated) to the PNGIMR laboratory where they were centrifuged at 10,000 g at 5 °C for 10 minutes. Saliva recovered after centrifugation was transferred to cryovials for storage. If no saliva was obtained after centrifugation, the sample was discarded. All blood products and saliva samples were initially stored at −80 °C at the PNGIMR before being shipped on dry ice to The Kids Research Institute Australia (formerly Telethon Kids Institute) in Perth, Western Australia, Australia.

Mothers were asked to self-collect vaginal swabs shortly after delivery using eNAT FLOQSwabs. These samples were used to collect information on the background prevalence of maternal vaginal carriage of probiotic species, in addition to pathogens associated with neonatal sepsis, such as group B *Streptococcus* and *Escherichia coli*, which may be vertically transmitted to the infant at the time of delivery. The swabs were stored at −80 °C.

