### Sample Size Calculation

It was determined that a sample size of 50 participants per group would achieve 90% power to detect a difference in colonization rates of 30% in the probiotic group versus 5% in the placebo group, using a 2-tailed test of proportions with continuity correction at the 5% significance level. A final sample size of 65 participants per group was decided upon, taking into account a presumed 10% loss to follow-up and difficulties in timely biosample collection. On the basis of this sample size, it was estimated that the study would have 80% power to detect a 50% reduction in pneumococcal colonization rate in the probiotic group versus the placebo group at the 5% significance level.

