### Statistical Analyses

The data will be cleaned before analysis. All data will be downloaded from REDCap and a backup copy archived before data cleaning. Missing data, outliers, and inconsistencies will be queried and verified against source documentation. Where data require changing, the database will be updated accordingly. All queries and corresponding amendments will be documented. Per-protocol and intention-to-treat analyses will be performed using available outcome data. The distribution of missing data across the treatment groups will be described, and reasons for missingness will be explored where possible to assess whether data are missing at random.

The primary objective is to determine the feasibility and safety of treatment. The number of solicited and unsolicited adverse events as well as the number of discontinued, missed, and completed doses will be summarized descriptively by treatment group. Pearson chi-square and Fisher exact tests will be used as appropriate to determine the significance of differences between groups.

The secondary objective is to measure gut colonization by probiotic strains on the last day of treatment (d 7-d 10) and at ages 1, 3, and 4 months. The prevalence of colonization at each time point will be summarized descriptively by treatment group. Colonization status, categorized as positive or negative, will be compared between treatment groups using the Pearson chi-square test, while continuous measures of colonization (ie, cycle threshold or relative fluorescence units) will be analyzed using 1-way ANOVA.

The exploratory objectives include measuring the hospitalization rates throughout the study; nasopharyngeal carriage of *S pneumoniae* and other respiratory bacteria; IgG antibody titers to PCV13, DTwP, Hib, and hepatitis B; the kinetics of probiotic gut colonization; and maternal carriage of probiotic species at the time of delivery.

Hospitalization rates will be reported descriptively per treatment group and compared using Pearson chi-square or Fisher exact tests as appropriate.

Nasopharyngeal carriage of *S pneumoniae* and other respiratory bacteria as well as gut colonization will be summarized descriptively at each corresponding time point. A Cox regression analysis will be performed, adjusting for birth weight, sex, previous antibiotic use, and breastfeeding status. Hazard ratios, along with their 95% CIs and *P* values, will be reported.

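### The between-group comparison of gut colonization leaves out the pre-dose rectal swab held for every infant, so native carriage can dilute the contrast and blur what colonized means

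*Protocol article*

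**What the plan says.** Study Design and Objectives states: "The secondary objective was to demonstrate the colonization of the gut by probiotic strains". In Methods, Specimen Collection, the list of sampling times begins "Rectal swabs were collected at enrollment; on the day of the last intervention administration (age 7-10 d" and continues to 6 months. The abstract places the first collection before the intervention, and Table 1 shows an enrollment rectal swab for 244 of 244 infants.

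Statistical Analyses names the last treatment day and ages 1, 3 and 4 months for this endpoint. The test is fixed as follows: "Colonization status, categorized as positive or negative, will be compared between treatment groups using the Pearson chi-square test". Cycle threshold or fluorescence is also compared, by one-way ANOVA. A Cox model, described straight after the sentence on nasopharyngeal carriage and gut colonization, adjusts for birth weight, sex, earlier antibiotic use and breastfeeding. Enrollment colonization status is not in that list. The same section plans ad hoc comparisons of antibody levels, nasopharyngeal carriage, SAEs and growth between colonized and non-colonized infants, with the same adjustment variables.

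The article expects some positivity that does not come from the product. The sample size is built on "a difference in colonization rates of 30% in the probiotic group versus 5% in the placebo group", and maternal swabs are collected for the "background prevalence of maternal vaginal carriage of probiotic species".

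**The concern.** An infant who was positive before the first dose cannot show that the product colonized the gut. If carriage exists at enrollment, post-dose status alone has four effects:

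- Every arm's colonization rate rises and the difference between arms shrinks, because only non-carriers can be converted.
- The prevalence reported within an active arm mixes native carriage with colonization by the product.
- In the colonization kinetics, a native carrier who stays positive looks like persistence of the product.
- In the colonized versus not-colonized analyses, which randomization does not protect, the colonized group combines infants who carried the organism from birth with infants the product colonized.

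The measurement that would address this has already been collected from every infant. The article prints the form of the endpoint, the visits, the test and the covariates, so a choice has been made and it leaves this measurement out.

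**Working it through.** **1. The plan's own figure.** Sample Size Calculation states that "a sample size of 50 participants per group would achieve 90% power", "using a 2-tailed test of proportions with continuity correction at the 5% significance level". With p1 = 0.30, p0 = 0.05 and unpooled variance:

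- n without correction = (1.960 + 1.282)² × (0.30×0.70 + 0.05×0.95) / 0.25² = 43.3
- n with correction = (43.3/4) × [1 + √(1 + 4/(43.3×0.25))]² = 51.0
- power at 50 per group = 89.3%

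The arcsine form gives 49.6 and the pooled form gives 55 (87.1% power at 50). The stated 50 reproduces, and it already includes 5% positivity on placebo.

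**2. Does omitting the enrollment swab create a false effect?** In 20,000 simulated trials per setting, with 56 per group, equal carriage in both arms and no product effect, the chi-square test rejected in 4.4%, 5.2% and 4.7% of trials at 5%, 20% and 40% carriage. The error rate is held.

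**3. Dilution.** Enrollment carriage q is not given, so 5% to 30% is assumed. Suppose carriers stay positive, no placebo non-carrier acquires the organism, and the product converts a fraction a of non-carriers. Setting a = (0.30 − 0.05)/0.95 = 0.263 reproduces the planned rates at q = 5%. Then:

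- placebo rate = q
- active rate p1 = q + (1 − q) × 0.263
- power = Φ{[(p1 − q) − 1/n − 1.96 × √(2p̄(1 − p̄)/n)] / √[(p1(1 − p1) + q(1 − q))/n]}, where p̄ = (p1 + q)/2 (pooled variance, continuity-corrected)

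Table 1 gives 233 rectal swabs at 8-10 days (233/3 ≈ 78 per arm) and 226 at 1 month (226/3 ≈ 75). It gives 179 and 177 at 3 and 4 months (179/3 ≈ 60 and 177/3 = 59). Counts by arm are not printed, so equal thirds are assumed.

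| q | Active v placebo | Difference (points) | Power, n = 50 | Power, n = 75-78 | Power, n = 59-60 | Active-arm positives already carriers (q/p1) |
|---|---|---|---|---|---|---|
| 5% | 30.0% v 5% | 25.0 | 87% | 98% | 93% | 17% |
| 10% | 33.7% v 10% | 23.7 | 76% | 92-93% | 83-84% | 30% |
| 20% | 41.1% v 20% | 21.1 | 54% | 75-77% | 63-64% | 49% |
| 30% | 48.4% v 30% | 18.4 | 39% | 57-59% | 46-47% | 62% |

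Worked line for q = 20%, n = 75: (0.2105 − 0.0133 − 1.96 × 0.0752)/0.0732 = 0.68, and Φ(0.68) = 0.75.

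**4. What the enrollment swab could recover.** Now let placebo non-carriers also become positive, at 5% against 30% on product, with carriage added on top. With 50 per group, unpooled variance and correction, 20% carriage gives 44% v 24%. Power is 49% using all infants. It is 80% using only the 50 × 0.80 = 40 enrollment-negative infants per arm. At 5%, 10% and 40% carriage the pairs are 79% and 88%, 68% and 85%, and 26% and 65%. The enrollment-negative analysis has more power each time despite using fewer infants.

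**The case against.** The strongest reply is that the concurrent, randomized, blinded placebo arm is itself the control for native carriage. A reader might infer that pre-dose carriers are credited to the product. For the between-group test the article does not support this: carriers count as positive in every arm, and step 2 shows the error rate holds. An unadjusted comparison of prevalence is valid, and the placebo arm also accounts for carriage acquired after 72 hours, which an enrollment swab cannot detect. All of this stands. What remains is lost precision in the test, and an interpretation problem for the within-arm rates, the kinetics and the unrandomized analyses.

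Two other stronger readings also go beyond the text:

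- That any positive qPCR counts as colonization by the product. No positivity cutoff is printed, and a cutoff may sit in a document not shown. Gut Colonization, under Laboratory Procedures, says both species and strains will be tested, and cycle thresholds are compared too. Whether the assays separate the product strain from wild carriage cannot be settled in either direction.
- That the enrollment swab is not used at all. Rectal swabs are to be tested, and the descriptive summaries by time point may include enrollment. What is absent is its use in the between-group comparison and the adjustment list.

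It is also fair to say that this is a secondary endpoint of a pilot, that carriage above 5% is an assumption, and that 50 per group understates the infants actually swabbed. Table 1 supports about 75 to 78 per arm at the first two analyzed visits. Power is correspondingly higher there, and it would be higher still under a Pearson test without correction.

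**Conclusion.** The point holds as a weakness of efficiency and interpretation, not as a bias in the randomized test. The planned comparison uses post-dose status only and omits a baseline value available for every infant.

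If enrollment carriage is near 5% and already contained in the placebo assumption, the planned 30% versus 5% is unchanged and little is lost. If carriage is 20% to 30%, power at the first two visits falls from about 98% to between 57% and 77%, and roughly half to three-fifths of active-arm positives would predate dosing. These figures assume that carriers stay positive at every visit, that placebo infants do not acquire the organism later, and that arms are equal in size; the article establishes none of these.

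The effect on the colonized versus not-colonized analyses cannot be quantified from the article, but no placebo comparison protects them. The change is worth making because it costs little and data analysis was still ongoing at publication.

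**What to change.** Keep the planned comparison of all infants, but adjust each visit's comparison for enrollment-swab status for the organism concerned, for example with a Mantel-Haenszel test stratified on it. Then:

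- add an analysis of acquisition, meaning positive at the visit among infants whose enrollment swab was negative for that organism;
- report enrollment prevalence of each organism by arm, and show the kinetics separately for enrollment-positive and enrollment-negative infants;
- account for enrollment status in the colonized versus not-colonized analyses, by adjustment or by separating pre-dose carriers;
- describe the result as species or subspecies carriage for any assay not shown to be strain specific.

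The cost is analysis wording, one added covariate or stratum, and a somewhat smaller denominator in the acquisition analysis. The enrollment swabs are already collected and stored.

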IgG antibody titers to PCV13, DTwP, Hib, and hepatitis B will be reported descriptively at baseline (before vaccination at age 1 mo) and at age 4 months (1 mo after the third dose). The differences between treatment groups will be estimated using linear regression, adjusting for birth weight, sex, breastfeeding status, and previous antibiotic use at each time point. The model will also adjust for maternal antibody titers to diphtheria, tetanus, and pertussis when comparing IgG titers to DTwP, using prevaccination infant titers as proxy measures. All IgG levels will be log transformed before analysis to meet the normality assumptions of linear regression analysis. The corresponding coefficients, along with their 95% CIs and *P* values, will be reported.

Maternal vaginal carriage of probiotic species will be reported descriptively and compared using the Pearson chi-square test.

Ad hoc analyses will include comparisons of IgG antibody levels, nasopharyngeal carriage of respiratory bacteria, SAEs, and other growth outcomes between participants colonized and those not colonized by *B longum* subspecies *infantis* or *L plantarum*. The Pearson chi-square test, the Fisher exact test, and regression modeling will be used as appropriate. The models will adjust for the variables specified earlier.

To ensure that normality assumptions are met before parametric testing, tests for normality (eg, the Shapiro-Wilk test) and a visual assessment of distribution using histograms will be carried out and the results reported. Where necessary (eg, antibody titers), the raw data will be log transformed to achieve a normal distribution.

The results of the analysis will be reported according to the CONSORT (Consolidated Standards of Reporting Trials) guidelines.

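### One-way ANOVA is fixed for continuous gut colonization without saying how qPCR-negative infants enter, and at the plan's own design rates it suits neither way of handling their Ct

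*Protocol article*

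**What the plan says.** The secondary objective is gut colonization by the probiotic strains. Under Statistical Analyses, positive/negative status is compared between arms by Pearson chi-square, "while continuous measures of colonization (ie, cycle threshold or relative fluorescence units) will be analyzed using 1-way ANOVA". No value or rule is given for a negative reaction in that ANOVA.

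The same section says: "Per-protocol and intention-to-treat analyses will be performed using available outcome data". It then turns to describing missing data by arm. Later it adds a precondition: "To ensure that normality assumptions are met before parametric testing, tests for normality (eg, the Shapiro-Wilk test" and histograms. The only remedy it names for non-normal data is log transformation. It names no rank-based, censored or two-part method for this outcome.

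The Sample Size Calculation section is built on "a difference in colonization rates of 30% in the probiotic group versus 5% in the placebo group", without a time point or species. The Gut Colonization section specifies a separate qPCR for each of the two species.

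**The concern.** A named test is attached to an outcome that, at the design rates, most infants would not show. There are two ways to put Ct into an ANOVA, and each has a defect.

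- **Only infants with a Ct.** Being in the analysis is then itself the outcome, so randomisation no longer protects the comparison. The placebo group is also very small.
- **Negatives set to a ceiling Ct.** Between 70% and 95% of values in an arm are then one constant. The plan's own normality check fails and no usable fallback is given.

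At stake is the interpretation of the continuous colonization result. On the first handling, the mean load could point towards placebo while the prevalence result points strongly the other way. On the second, the analyst would have to break the plan's stated condition or choose another test after seeing the data.

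**Working it through.** **1. The design figure.** Inputs from Sample Size Calculation: 30% v 5%, two-sided 5%, 90% power, continuity correction, 50 per group.
- Unpooled variance: n = (1.960 + 1.282)² × (0.30×0.70 + 0.05×0.95) / 0.25² = 43.3. After continuity correction, (43.3/4) × [1 + √(1 + 4/(43.3×0.25))]² = 51.0.
- Pooled variance gives 47 without and 55 with the correction.

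The stated 50 is close to the unpooled version, so 30% and 5% are the rates the design rests on.

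**2. Share of non-detects.** 1 − 0.30 = 70% in the matching synbiotic arm and 1 − 0.05 = 95% in placebo. If the non-matching synbiotic arm carries the species at the placebo rate (assumption), the overall share is 1 − (0.30 + 0.05 + 0.05)/3 = 87%.

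**3. Infants with a Ct.** Expected number = rate × infants per arm. Swab counts are from Table 1, and an equal split between arms is assumed.

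| Basis | Per arm | Matching arm | Placebo (and non-matching arm) |
|---|---|---|---|
| Power calculation | 50 | 15.0 | 2.5 |
| First target | 65 | 19.5 | 3.3 |
| Expanded target | 80 | 24.0 | 4.0 |
| Last-dose visit, 233 swabs | 77.7 | 23.3 | 3.9 |
| 1 month, 226 swabs | 75.3 | 22.6 | 3.8 |
| 3 months, 179 swabs | 59.7 | 17.9 | 3.0 |
| 4 months, 177 swabs | 59.0 | 17.7 | 3.0 |

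With 75 infants at 5%, P(at most one positive) = 0.106. With two such arms, the chance that at least one has fewer than two positives is 1 − (1 − 0.106)² = 0.20.

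**4. Positives-only ANOVA.** From the noncentral F distribution, with 22, 4 and 4 infants, power for a 1-SD difference in Ct between the matching arm and the other two is about 52%.

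Simulation used 75 per arm, rates 30%/5%/5%, Ct SD 3 and 4,000 trials; the Ct values are assumptions.
- Equal load among positives (mean Ct 30 in every arm): the ANOVA rejects in about 5% of analysable trials. This is correct size, because load among positives really is equal.
- Lower load in matching-arm positives (mean Ct 32 v 29; a higher Ct means a lower load): it rejects in about half of analysable trials, nearly always with the mean favouring placebo, although six times as many matching-arm infants are colonized.

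**5. Ceiling-coded ANOVA (negatives set to Ct 40, an assumption).**
- Size with equal rates in all arms: about 4% when all are at 5%, and about 5% when all are at 30%.
- Power in the equal-load scenario: about 99%, the same as Kruskal-Wallis on all infants. In the lower-load scenario: about 95%, against over 99% for Kruskal-Wallis.
- Normality: with positives at mean 28, SD 4, Shapiro-Wilk gives p < 1e-11 in both a 30% and a 5% arm, before and after log transformation.

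**6. The binary comparison.** Pearson chi-square on status rejects in about 99% of the same simulated trials.

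**The case against.** The strongest reply is that nothing says negatives are dropped. The sentence on available outcome data concerns missing data, and a swab that tests negative is an available result. A reader might infer that the protocol commits to comparing about 22 colonized infants with about 4. The documents do not support that: positives-only is one reading, and the ANOVA has three arms. Relative fluorescence units are also allowed, and these can be recorded for a negative reaction, so the no-value argument applies to Ct only. All of this stands.

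A reader might also infer that the trial would miss a real colonization effect. That does not follow. The same sentence of the protocol tests prevalence by chi-square, which detects the assumed difference almost always. The roughly 5% rejection rate of the positives-only ANOVA under equal load is correct size, not lost power. With ceiling coding, ANOVA is close to the rank test in power and holds its size.

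It can further be said that 30% and 5% are design inputs without a time point, so the counts are illustrative; if colonization proves much higher, the problem shrinks. That is right, and is why the range is shown.

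Last, the coding of non-detects is commonly left to an analysis plan or laboratory procedure. Its absence here would not be a finding by itself. But the article does fix the test, the precondition and the only named remedy, and at the design rates these do not fit together under either handling of Ct.

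**Conclusion.** The point holds in limited form. The protocol fixes one-way ANOVA for continuous colonization and leaves the entry of negatives open. At its own design rates, one handling of Ct gives a small, outcome-selected comparison: about 22 v 4 v 4 at 1 month, and about 15–24 v 2.5–4 across the plan's sample sizes and visits. The other handling fails the plan's normality condition with no workable remedy.

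The harm is confined to the interpretation of a positives-only result and to a precondition with no fallback. The feasibility and safety objectives and the binary colonization comparison are not affected. The counts rest on the 30% and 5% rates applying at the visit in question, an equal split of swabs between arms, and the non-matching arm behaving like placebo. The simulated rejection rates rest in addition on the assumed Ct distributions.

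**What to change.** For each species and visit, replace the ANOVA by a rank-based test on all infants with a tested swab: Kruskal-Wallis across the three arms, or Wilcoxon rank-sum of each synbiotic against placebo. Tie all non-detects at the lowest load and state that rule. Report load among positives descriptively only, with the number of infants behind each figure.

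A left-censored (Tobit) model is not needed. It would treat negatives as low values from the same normal distribution as positives, and may fit poorly at 70% to 95% censoring.

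The article reports that data analysis is still ongoing. The change needs no new data or assays, only analysis wording. The cost is that the effect is expressed on ranks and not as a difference in mean Ct.
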